## Abstract

**Background:** Adverse childhood experiences (ACE) can have negative effects on cognitive, social and emotion regulation abilities, which can threaten the child’s school integration and capacity to learn. While steady relations to sensitive, understanding adults may moderate these negative outcomes, the difficulties of children with ACEs pose a major challenge for teachers, whose insufficient preparation may lead to career attrition.

**Objective:** Psychoeducational trauma-informed care (TIC) interventions targeting teachers may strengthen teacher preparation and buffer the deleterious outcomes of ACEs, yet the evidence-base for these interventions is limited. Importantly, while minority groups are overrepresented among those with ACEs and additionally risk exposure to ethno-racial trauma, TIC interventions lack a social disadvantage/discrimination perspective. The Present trial addresses these issues.

**Method:** The study protocol employs a quasi-experimental design for assessing effects of a psychoeducational TIC intervention carried out in Swedish schools by Save the Children, Sweden (SCS). We compare, for the first time, an intervention group (*N* = 160) and a control group (*N* = 160) over time (pre-intervention, immediately after, 6 and 12 months post-intervention), assessing teacher stress, compassion fatigue, self-efficacy and trauma-informed knowledge. We monitor teacher attitudes and attributions of students’ academic weaknesses and behavioural and mental difficulties. The trial is preregistered (DOI:10.17605/OSF.IO/V7SH8).

**Results:** We hope that the mitigating effects of the SCS-TIC school intervention may be independent of social category, and that the trial will additionally generate knowledge of how providers and recipients of TIC may respond to it differently depending on their social and cultural identities. As school-based TIC practices and interventions are expansively relied on as means of preventing teacher burnout and career attrition, and buffering negative consequences of ACEs for children, establishing their effects with methodological robustness is important and timely.

**Conclusion:** Such knowledge may be used to tailor and target interventions to specific populations, while ensuring maximum effectiveness.

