### Aims and objectives of the planned study

1.4.

Despite paucity of empirical evidence of the effectiveness of TIC interventions, clinical research data indicate that an increased knowledge among caregivers concerning trauma and TIC practices leads to changed TIC attitudes (Brown et al., 2012). A recent meta-analysis of TIC interventions within the child welfare system indicated that caregivers reported reduced child PTSD symptoms and behavioural problems but only moderate improvement on children’s wellbeing (Zhang et al., 2021). However, while recent international studies regarding trauma-focused interventions are encouraging (Angelöw et al., 2023; Izzo et al., 2016; Purvis et al., 2015), most evaluations of TIC interventions suffer from methodological shortcomings and lack robust methods such as a control group or longer-term follow ups (Fondren et al., 2020; Hanson & Lang, 2016). In a school setting, the Three pillars intervention directed at teachers (Bath et al., 2021) has never been evaluated.

Therefore, the purpose of this study is to assess the effect of psychoeducational interventions in trauma-informed care directed at teachers. Building on the limited existing empirical evidence (MacLochlainn et al., 2022; Zhang et al., 2021) we expect that, after training in TIC, participants will report changed attitudes toward trauma-informed care and related practices (H1). These effects will be associated with increased perceived teacher efficacy, classroom management strategies (H2). Moreover, we expect decreased reported burnout and compassion fatigue symptoms (H3). Finally, we expect that these effects will be present also 6-months post-training (H4). Due to the underexplored nature of psychoeducational TIC interventions in terms of interactions with awareness about ethno-racial trauma and community specific experiences of ACEs, we refrain from making predictions concerning how the intervention might influence awareness about such socioeconomic and intersectional aspects of ACEs and trauma.

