### Primary outcome measures

2.5.

Levels of stress and compassion fatigue are measured by the Professional Quality of Life scale (PROQOL 5: Stamm, 2009), which examines the potential impact from helping others who have experienced trauma and adversities. The scale consists of 30 items divided into three subscales (Compassion satisfaction, *α* = .88, Burnout, *α* = .75 and Compassion fatigue, *α* = .81), with high internal consistency (Stamm, 2010).

Teacher self-efficacy in the classroom environment is measured by the Teachers’ Sense of Efficacy Scale (TSES: Klassen et al., 2014), addressing the distinct domains of pupil engagement, instructional practices and classroom management, with high internal consistency (*α* = .86; Klassen et al., 2014).

The Knowledge and Beliefs’ Survey (KBS: Murray, 2014) assesses self-efficacy, tolerance of child misbehaviour and knowledge of trauma-informed care and consists of 33 items and three subscales (Trauma-Informed Parenting, Tolerance of Misbehaviour, and Parenting Efficacy), all with satisfactory internal consistency (Cronbach’s a .75–.83; Murray, 2014; Sullivan et al., 2016). KBS is commonly used for assessment in the foster care setting. Here, we use a subset of 17 items, adapted to apply in the school setting (e.g. *I routinely think about how students with traumatic experiences are physically safe at our school, but might not feel safe*). The 16 items that specifically concerned out-of-home care (e.g. *I feel confident talking with my child about his/her feelings about his/her biological parents*) were removed.

Awareness about intersectional disparities concerning how ACEs affect individuals and the potential traumatic experiences of racism and discrimination is operationalised utilising three different constructs:

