### Power/sample size calculations, data analysis plan and attrition analyses

2.7.

A power analysis employing R and G*Power with an aimed .80 power, significance level of .05 and an effect size of *d* = .5, yielded a sufficient sample size of *N* = 99 for our basic analyses. Estimating a drop-rate of about 40% over time, perhaps even higher for the control group, we determined a target sample size of *N* = 160 for the experimental group and *N* = 160 for the control group.

Data from all measures will be analysed using R (R Core Team, 2021) and JAMOVI (The Jamovi Project, 2022). Attrition analyses will be conducted, and missing data among participants who have completed all four measurements will be handled either utilising multiple imputation or by applying maximum likelihood estimation when employing the mixed linear model analysis. Independent *t*-tests will assess potential differences between experiment and control group concerning outcome measurements (e.g. perceived teacher efficacy, classroom management strategies, burnout and compassion fatigue symptoms) at baseline. For hypothesis testing, we will employ mixed linear model analyses of repeated measures to estimate fixed (i.e. the trauma-informed care training) and random (e.g. participants’ social class, gender, ethnicity) effects of training on the study outcome variables, comparing both within individuals (repeated measures analysis) and between groups (experimental versus control group measures at each timepoint). Interaction factors in the models are used for estimating potential moderation by ethnicity, socioeconomic status and other characteristics. For example, a three-way interaction of gender, ethnicity and social-class may uncover intersectional outcomes particularly for women with non-Swedish backgrounds that might indicate a heightened trauma-informed care approach to vulnerable students independently of whether they are in the experimental or control group.

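### All six instruments are labelled primary, although the protocol makes no prediction for three of them and states no order or alpha sharing

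*Protocol article*

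**What the plan says.** Section 2.5 of the protocol article is headed "Primary outcome measures". It is the only section on outcomes; section 2.6 covers background variables. Six instruments stand under that heading:

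- the Professional Quality of Life scale (ProQOL): "Levels of stress and compassion fatigue are measured by the Professional Quality of Life scale"
- the Teachers' Sense of Efficacy Scale (TSES): "Teacher self-efficacy in the classroom environment is measured by the Teachers’ Sense of Efficacy Scale"
- the Knowledge and Beliefs Survey (KBS), cut to 17 adapted items; the parent version "assesses self-efficacy, tolerance of child misbehaviour and knowledge of trauma-informed care and consists of 33 items and three subscales"
- three awareness measures, introduced by "Awareness about intersectional disparities concerning how ACEs affect individuals and the potential traumatic experiences of racism and discrimination is operationalised utilising three different constructs": a scale of attributions of academic achievement, a scale of attributions of mental health, and the Modern Racism Scale.

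Section 1.4 sets out four hypotheses. H1 concerns trauma-informed attitudes and practices, H2 teacher efficacy and classroom management, H3 burnout and compassion fatigue, and H4 persistence at six months. On the awareness construct it says "we refrain from making predictions concerning how the intervention might influence awareness about such socioeconomic and intersectional aspects of ACEs and trauma". The abstract draws a similar line. It lists stress, compassion fatigue, self-efficacy and knowledge as what is assessed, and then adds "We monitor teacher attitudes and attributions of students’ academic weaknesses and behavioural and mental difficulties".

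Section 2.7 gives a "significance level of .05" as an input to the power analysis. No other alpha appears in the article.

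**The concern.** A primary label tells readers which results answer the trial's main question. Here it covers measures for which the authors expressly hold no expectation. Since no direction is predicted, a shift on the Modern Racism Scale either way would count as a result on a primary outcome, yet it would bear on none of H1 to H4. With six co-equal primaries and no stated rule across them, the article does not say what pattern of results would show that the training worked. It also does not say how the chance of a false primary claim is held near 5%.

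This is more than a detail left to a fuller document. The article itself assigns the tier, and assigns it in conflict with its own section 1.4.

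**Working it through.** **1. The passages side by side.**

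| Instrument | Section 2.5 | Section 1.4 | Abstract |
|---|---|---|---|
| KBS | primary | H1 (closest match) | assessed |
| TSES | primary | H2 | assessed |
| ProQOL Burnout, Compassion fatigue | primary | H3 | assessed |
| Two attribution scales | primary | no prediction | monitored |
| Modern Racism Scale | primary | no prediction | monitored, if attitudes is read to include it |

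ProQOL Compassion satisfaction is described in 2.5 but appears in no hypothesis. The twelve-month visit (T4) also has none, because H4 stops at six months.

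**2. The plan's own figure.** Section 2.7 gives N = 99 for d = .5, power .80 and alpha .05, without stating sidedness or whether 99 is a total or per group.

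- Two-sided .05: n per arm = 2 × ((1.960 + 0.842)/0.5)² = 62.8, so 63 per arm and 126 in total (exact t test: 64 and 128). This does not give 99.
- One-sided .05: total = 4 × ((1.645 + 0.842)/0.5)² = 98.9, which matches 99 as a total (exact t test: 102).
- Two-sided .05/6, exact t test: 98.6, which matches 99 per arm. The per-arm reading fits the inflation to 160 per group approximately (99/0.6 = 165).

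The text does not settle which was used, so the alpha intended for each outcome cannot be recovered from the sample size.

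**3. Chance of at least one false-positive primary result,** with each outcome tested once at .05 and no true effects:

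- Six instruments, independent: 1 − .95⁶ = 26.5%.
- Six instruments, common correlation assumed (simulated equicorrelated normal statistics): 24% at .3, 21% at .5, 17% at .7, 11% at .9.
- Three predicted instruments, independent: 1 − .95³ = 14.3%.
- Four predicted scores (KBS, TSES, Burnout, Compassion fatigue), independent: 1 − .95⁴ = 18.5%.

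**4. After control across the four predicted scores.** With Bonferroni at .05/4 = .0125, the error rate is 1 − .9875⁴ = 4.9%. Holm controls it at 5% with at least as much power.

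**5. What sharing costs in power.** With 160 per group and 40% dropout, 160 × 0.6 = 96 remain per group. At d = .5 the expected test statistic is 0.5 × √(96/2) = 3.464.

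- Two-sided .05: Φ(3.464 − 1.960) = 93%.
- Two-sided .0125: Φ(3.464 − 2.498) = 83%.

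These figures use a normal approximation, ignore clustering by school or training group, and assume that d = .5 applies to every outcome.

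**The case against.** The strongest reply is that this is a condensed article. A preregistration exists and an analysis plan may exist, and multiplicity handling is commonly placed there. The .05 is only a power input. A reader might infer that every outcome will be tested at an unadjusted .05, but the document never says so, and the match of 99 per arm with .05/6 shows why it should not be asserted. That match may itself be coincidence. This part of the reply stands: the error rates above are conditional on how the tests are run.

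A reader might also count every subscale: 3 ProQOL, 3 TSES, 3 KBS, 1 achievement, 2 mental-health and 1 racism score make 13, or 39 across three follow-ups. For independent tests 13 scores give 1 − .95¹³ = 48.7%, and 39 give 1 − .95³⁹ = 86%. The text does not support these counts as primary tests. It describes subscales without saying that each is tested, does not say that the shortened KBS keeps three subscales, and places the timepoint comparisons within a repeated-measures model. Repeated scores on the same people are also far from independent.

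Finally, H1 to H4 and the abstract already signal that the awareness measures are not confirmatory, and a primary outcome may be tested two-sided without a directional prediction. Both points are fair. They show that the label is careless rather than impossible, but they do not remove the conflict. If the authors regard these measures as exploratory, section 2.5 says otherwise.

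**Conclusion.** The point holds as a contradiction within the article. Section 2.5 makes six instruments primary with no lower tier, while section 1.4 makes no prediction for three of them and the abstract only monitors that area. No order or sharing of alpha across the primaries is stated.

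If each instrument is tested once at .05, the chance of at least one false-positive primary result is 26.5% under independence and about 21% at an assumed correlation of .5. That is roughly four to five times the nominal 5%. Separate tests of subscales or timepoints would raise it. It would be going too far to call a chance primary success likely, since at instrument level the figure stays near one in four or below. The contradiction itself rests on no numerical assumption. The size rests on one test per instrument at .05, no true effects and the assumed correlation.

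**What to change.** - **Relabel as exploratory,** reported with confidence intervals: the two attribution scales, the Modern Racism Scale, any subscale not named in H1 to H3 (such as Compassion satisfaction), and T4.
- **Restrict the primary set** to the outcomes that test H1 to H3: KBS, TSES, and ProQOL Burnout and Compassion fatigue. State the score used for each.
- **Control the error rate across that set,** for example with Holm or a prespecified order. H1 to H4 is one option, but the investigators should choose: nothing in the article makes KBS the gatekeeper, and in a fixed order a null first result would block formal testing of burnout.
- **Name the visit that tests H4.** Section 1.4 counts six months from training, while section 2.2 counts T3 from baseline.
- **State the alpha and sidedness behind N = 99,** and whether it is a total or per group.

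The cost is relabelling and a registration update, with no new data. Fewer results can be called confirmatory. If alpha is split equally over four scores, power per outcome falls from about 93% to about 83% at the planned size after dropout, under the assumptions shown, and by less with Holm.

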### Background variables

2.6.

Background variables will include participants’ age, mother language, gender, profession, work experience, ethnicity, and social class.

### Power/sample size calculations, data analysis plan and attrition analyses

2.7.

A power analysis employing R and G*Power with an aimed .80 power, significance level of .05 and an effect size of *d* = .5, yielded a sufficient sample size of *N* = 99 for our basic analyses. Estimating a drop-rate of about 40% over time, perhaps even higher for the control group, we determined a target sample size of *N* = 160 for the experimental group and *N* = 160 for the control group.

Data from all measures will be analysed using R (R Core Team, 2021) and JAMOVI (The Jamovi Project, 2022). Attrition analyses will be conducted, and missing data among participants who have completed all four measurements will be handled either utilising multiple imputation or by applying maximum likelihood estimation when employing the mixed linear model analysis. Independent *t*-tests will assess potential differences between experiment and control group concerning outcome measurements (e.g. perceived teacher efficacy, classroom management strategies, burnout and compassion fatigue symptoms) at baseline. For hypothesis testing, we will employ mixed linear model analyses of repeated measures to estimate fixed (i.e. the trauma-informed care training) and random (e.g. participants’ social class, gender, ethnicity) effects of training on the study outcome variables, comparing both within individuals (repeated measures analysis) and between groups (experimental versus control group measures at each timepoint). Interaction factors in the models are used for estimating potential moderation by ethnicity, socioeconomic status and other characteristics. For example, a three-way interaction of gender, ethnicity and social-class may uncover intersectional outcomes particularly for women with non-Swedish backgrounds that might indicate a heightened trauma-informed care approach to vulnerable students independently of whether they are in the experimental or control group.

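### The sample-size statement in section 2.7 is not internally consistent: N = 99 does not follow from its stated inputs by a standard two-sided test, and the step from 99 to 160 per group does not fit a 40% loss

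*Protocol article*

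**What the plan says.** Section 2.7 (Power/sample size calculations, data analysis plan and attrition analyses) describes a power analysis in R and G*Power "with an aimed .80 power, significance level of .05 and an effect size of" d = .5. It reports that this "yielded a sufficient sample size of *N* = 99 for our basic analyses". It then allows for loss to follow-up and sets the target: "Estimating a drop-rate of about 40% over time, perhaps even higher for the control group, we determined a target sample size of" 160 in the experimental group and 160 in the control group.

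The section does not say whether 99 is per group or in total, whether the test is one- or two-sided, or which test counts as a basic analysis. It states no within-person correlation and no adjustment of alpha. The same section assigns independent t-tests to baseline comparisons and mixed linear models of repeated measures to the hypotheses. Section 2.2 gives four measurement occasions.

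**The concern.** The article gives every figure in the chain: power, alpha, effect size, required N, loss and target. A reader can therefore check the chain, and with a standard two-group test it breaks at two places. The required N does not come from the stated effect size, and the target does not come from the required N at the stated loss.

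What is at stake is interpretation. If 99 is per group, the figure behaves like a calculation for d = .40. If it is a total, it behaves like a one-sided calculation or one that borrows strength from repeated measures. These imply different smallest effects that the trial was designed to detect, and so different readings of a null result.

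**Working it through.** **Inputs, all from section 2.7.** d = .5, so difference 0.5 with SD 1; power .80; alpha .05; stated N = 99; loss about 40%; target 160 + 160.

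**1. Two-sided two-group comparison at d = .5.**
- Normal approximation: n per group = 2(1.960 + 0.842)² / 0.5² = 62.8, so 63 per group and 126 in total.
- Two-sample t-test (noncentral t): 63.8, so 64 per group and 128 in total.
- Neither the per-group figure nor the total is 99.

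**2. Reading 99 as per group.**
- Two-sided power at d = .5 with 99 per group is 0.94, not .80.
- 80% power with 99 per group corresponds to d = .40, for which the t-test requirement is 99.08 per group.
- Retained sample: 160 × (1 − 0.40) = 96, which is 3 below 99.
- Target needed to keep 99: 99 / 0.60 = 165 per group.
- Loss that takes 160 to exactly 99: 1 − 99/160 = 38.1%.

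**3. Reading 99 as a total (49.5 per group).**
- Two-sided power at d = .5 is 0.69.
- One-sided normal approximation: total = 4(1.645 + 0.842)² / 0.25 = 98.9, which matches 99.
- One-sided t-test: 50.2, so 51 per group and 102 in total, which does not match.
- Repeated-measures ANOVA, between-group test, f = .25, with an assumed correlation r (none is stated): four measurements give 99 at r = .69 and 100 at r = .7; two measurements give 97 at r = .5.
- Baseline-adjusted comparison (ANCOVA) with assumed r = .5: 2 × 63.77 × (1 − 0.25) = 95.7, so 96 in total.
- Inflating a total of 99 for 40% loss gives 99 / 0.60 = 165 in total, about 83 per group. It does not give 160 per group.

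**4. A per-group route at d = .5.** Splitting alpha over six outcomes (.05/6 = .0083, two-sided) gives 98.6, so 99 per group. Section 2.5 lists six instruments as primary, but no adjustment is stated anywhere.

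**5. What the target delivers for d = .5 (two-sided .05, unadjusted, no clustering).**

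| Retained per group | Loss from 160 | Power at d = .5 | d with 80% power |
|---|---|---|---|
| 96 | 40% | 0.93 | 0.41 |
| 80 | 50% (illustration of heavier loss) | 0.88 | 0.45 |
| 64 | 60% | 0.80 | 0.50 |

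**The case against.** The strongest reply is that 99 may be a correct answer to a calculation that the article has condensed. The hypotheses are tested by repeated-measures models, not by an unadjusted t-test, and several hypotheses in section 1.4 are directional. A four-measurement design at r = .69, a one-sided normal approximation or a six-way alpha split each gives 99 at d = .5. A condensed article may leave such details to a fuller plan. This stands in part. It would be wrong to say that 99 cannot be right for d = .5, or that every reading contains an error. What can be said is that 99 does not reproduce from the stated inputs by the standard two-sided test, and that each route to it needs an assumption that the article does not state. The routes that give a total also leave 160 per group unexplained.

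A second reply is that 96 against 99 is only rounding: the loss is given as approximate, and 38.1% would leave exactly 99. This also stands in part. The shortfall exists only if 99 is per group, and it is three people. But the same sentence expects control loss to be possibly higher than 40%, so the rounding goes the wrong way for that group.

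A reader might infer that the trial is too small. The documents do not support this for d = .5: the retained 96 per group is well above 64, and even 80 per group gives 0.88. Clustering of participants within schools and training groups would lower these figures, but that is a separate issue and adds nothing to this one.

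**Conclusion.** The point holds as an inconsistency in reporting, not as a shortage of participants. With the stated d, alpha and power, a two-sided two-group test needs 64 per group (128 in total), not 99. The per-group reading, which the step to 160 suggests, fits d = .40 unless an unstated alpha split is supposed, and it is missed by three at 40% loss. The total reading has 69% two-sided power unless sidedness or a correlation is assumed, and it does not lead to 160 per group.

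The power figures for the retained sample (0.93 at 96 per group, 0.88 at 80) rest on a two-sided alpha of .05, no alpha adjustment, independent participants and equal loss in both groups. The 50% loss is an illustration; the article gives no number for the heavier control loss. Severity is minor to moderate: the recruitment target can stand, but the reader cannot tell which effect the trial was sized for.

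**What to change.** Keep 160 + 160 and restate the calculation so that its parts agree: effect size, test, sidedness, whether N is per group or total, any assumed correlation or alpha adjustment, required N, loss and retained sample.

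If the basis is a two-sided two-group test, the text could read: *With two-sided alpha .05 and 80% power, 64 participants per group are required for d = .5. Recruiting 160 per group with 40% loss leaves 96 per group, giving about 93% power for d = .5, or 80% power for d = .41, before allowance for clustering.*

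If 99 came from another calculation, that calculation should be reported rather than replaced by the simpler one. If 99 per group is kept, give its actual basis (for example d = .40, or an alpha split) and say that 40% loss leaves 96. If 99 is a total, state the sidedness or correlation behind it and explain separately why 160 per group was chosen.

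The cost is a reworded paragraph and one recalculation. No extra participants and no change to data collection are needed.

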Crucially, although empirical work has demonstrated how early adversities might affect individuals differently, emphasising the risk of additional burden from social inequalities and discrimination and proposing models of healing from ethno-racial trauma (Bernard et al., 2021; Chavez-Dueñas et al., 2019), the conventional TIC-framework is lacking behind in incorporating these perspectives (Saleem et al., 2020). Notably, studies that employ expanded ACE frameworks, that encompass potentially traumatic events relevant to experiences among ethnic and racially diverse minorities, demonstrate that these frameworks are more endorsed by members of minority groups compared to non-minority groups (Cronholm et al., 2015), and result in more accurate reports of ACEs from children and youth from minority groups (Maguire-Jack et al., 2020). Thus, understanding how social inequalities and discrimination may interact with the outcomes of TIC intervention is essential, as interventions may be futile for children in critical need of receiving adequate support if their calls for help are not recognised as expressions of trauma.

Despite the trial’s rigorous design, we acknowledge certain methodological limitations. The absence of intervention for the control group is a weakness. Additionally, participants may report positive trauma-informed attitudes as a result of self-fulfilling prophecies to enhance the effects of training. As schools and school teachers invest substantial resources in terms of time, energy, commitment in TIC, and related work structures in the school, another potential source of bias is from ‘escalation of commitment’ denoting the tendency to declare continued commitment in endeavours invested in. Importantly, the trial focuses on the perspective of the teachers as providers of TIC. Research has demonstrated that teachers may not always ‘practice what they preach’, and reported beliefs, attitudes and behaviours may thus not be aligned with the lived experiences of the students (Mansour, 2013; Tobin et al., 1994). Lastly, given the trial longitudinal design, participant attrition may pose a threat to the data.

Since the decision of which schools will be given TIC-training is preset by the Swedish government, it is not possible to guarantee full randomisation.

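### The missing-data method is limited to participants with all four measurements, so as written it does not reach the roughly 40% who are expected to drop out

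*Protocol article*

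**What the plan says.** Section 2.7 of the protocol article promises attrition analyses and then fixes the scope of the missing-data method: "missing data among participants who have completed all four measurements will be handled either utilising multiple imputation or by applying maximum likelihood estimation". The likelihood option is tied to the mixed linear model, which is also the model for hypothesis testing.

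The sample-size paragraph of the same section gives the expected loss: "Estimating a drop-rate of about 40% over time, perhaps even higher for the control group". The power calculation "yielded a sufficient sample size of *N* = 99 for our basic analyses", and after the dropout allowance "we determined a target sample size of *N* = 160 for the experimental group and *N* = 160 for the control group".

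The Discussion concedes that "given the trial longitudinal design, participant attrition may pose a threat to the data" but offers no remedy. Section 2.3 separately excludes people who do not complete the training programme. Nothing in the article extends imputation or likelihood estimation to participants who miss a measurement occasion.

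**The concern.** Someone who has completed all four measurements has, by definition, no missed wave. The only data such a person can lack are items or scales within a returned questionnaire. The larger loss that the protocol predicts is whole waves from people who leave, and the stated method stops short of it.

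Two things are at stake:

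- **Bias.** If those who stay differ in outcome from those who leave, and this differs between arms, a completer comparison mixes the training effect with selection. The protocol itself raises the possibility of unequal dropout. Burnout is among the outcomes, so outcome-related dropout is plausible. The arms are not randomised either.
- **Unused data.** A person who answers T1, T2 and T3 but misses T4 would contribute nothing. Yet H1 to H3 concern effects after training, and H4 concerns six months, which T3 is meant to serve. None of the four hypotheses needs the 12-month wave.

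**Working it through.** **1. The plan's own figure.** Inputs from section 2.7: power 0.80, significance level 0.05, d = 0.5, N = 99. Whether the test is one- or two-sided, and whether 99 is a total or per group, is not stated.

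- One-sided, two equal groups, normal approximation: total = 4 × ((1.6449 + 0.8416)/0.5)² = 98.9, so 99 in total.
- Two-sided: 63 per arm, 126 in total, which does not match.

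So 99 reproduces as a one-sided total.

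**2. What the dropout allowance was sized for.** 160 × (1 − 0.40) = 96 per group. Going from 160 to 99 is a loss of 38.1%, about 40%. The allowance therefore appears to treat 99 as a per-group number and to leave about that many completers in each group. This is generous rather than short, and it fits an analysis of completers.

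**3. How many fall outside the method.** 320 × 0.40 = 128 participants, 64 per arm, or more if control dropout is higher.

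**4. Size of the bias, simple selection model.** Assumed: correlation 0.3 between the tendency to remain and the outcome, the same in both arms; retention 60% in the trained arm and 50% in controls. The shift in an arm's completer mean, in SD, is 0.3 × φ(z)/p, where p is the retention and z its normal quantile.

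- Trained, p = 0.6: 0.3 × 0.644 = 0.19
- Control, p = 0.5: 0.3 × 0.798 = 0.24
- Net effect on the difference: 0.19 − 0.24 = −0.05

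**5. Size of the bias, simulation.** From the plan: 160 per arm, about 40% dropout, d = 0.5. Assumed: correlation 0.6 between all occasions, and T3 and T4 missing with a probability that depends on the observed T2 score. There were 3,000 replicates. The quantity is the group difference in T4 means.

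| Dropout scenario | True difference | Completers | Likelihood, all available data |
|---|---|---|---|
| Unrelated to score, 40% in both arms | 0.5 | 0.50 | 0.50 |
| Related to score, same rate and mechanism | 0.5 | 0.50 | 0.50 |
| Same mechanism, 40% trained, 50% control | 0.5 | 0.46 | 0.50 |
| Related to score in trained arm only | 0.5 | 0.62 to 0.70 | 0.50 |
| Related to score in trained arm only | 0 | 0.11 to 0.21 | 0.00 |

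The third row agrees with step 4. The simulation has one limit. With equal correlations, selection that moves completers' T2 mean by δ moves both their T1 and T4 means by 0.6δ, so a contrast of change from baseline would shift by 0.6δ − 0.6δ = 0. The table therefore applies to the comparison of groups at a timepoint, which section 2.7 names, and not to every contrast a completer mixed model could report.

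**6. Unused data.** Assumed: a steady 15% loss at each follow-up, since 0.85³ = 0.61 is close to 60% retained. Per arm, 160 × 0.85 = 136 have T2 data and 160 × 0.614 = 98 have all four waves. Unused T2 records: (136 − 98)/136 = 28%. Cross-sectional standard error ratio: √(136/98) = 1.18. Another dropout pattern gives other figures.

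**7. Power.** Two-sided, individual-level, no clustering: Φ(0.5 × √(n/2) − 1.96). This gives 93% with 96 per arm and 89% with 80 per arm.

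**The case against.** The strongest defence is that the sentence describes how missing data are handled and does not define an analysis set. The only stated exclusion is of programme non-completers. Mixed models for repeated measures ordinarily use partial records, and section 2.7 plans comparisons at each timepoint. The phrase may be a drafting slip: within-questionnaire gaps to be imputed, dropout to be examined in the attrition analyses. Part of this stands. A reader might infer that dropouts are certain to be discarded, but no sentence says so; that is an inference from the scope phrase and from the sizing in step 2. What does not stand is that the text is harmless. It attaches the restriction to the likelihood option as well, and attrition analyses do not repair estimates.

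A reader might also infer that completers have almost nothing missing. The documents give no item non-response rate, and the battery is long: 30 + 17 + 8 + 16 + 9 = 80 items before the teacher efficacy scale, repeated four times. Imputing within waves may be worthwhile; it is simply not enough.

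On size, a reader might take the shift of about 0.2 SD within each arm as the bias. The shifts largely cancel, and the relevant figure under those inputs is about 0.05 SD, a tenth of d = 0.5. The larger errors in step 5 need outcome-related dropout in the trained arm only. The documents give no direct support for that pattern; if anything they expect more dropout among controls.

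**Conclusion.** The point holds as a stated rule with the wrong scope. As written, the method covers only gaps within completed waves, implies a four-wave completer analysis, and leaves about 128 of 320 participants outside it.

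Bias is a risk and not a certainty. It would be too strong to say that a completer analysis is valid only if dropout is unrelated to outcome: when rate and mechanism are equal in both arms, the between-group contrast is unbiased. Under the assumed correlation of 0.3 and retention of 60% against 50%, the net bias is about 0.05 SD. If the mechanism differs between arms it can be larger, up to about 0.2 SD in the illustrative scenarios for the T4 difference. All the dropout mechanisms are assumptions; from the documents come only the sample size, the dropout of about 40%, the possible excess in controls and d = 0.5.

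The loss of T2 and T3 data is real under this reading, but its size depends on the dropout pattern, and power at d = 0.5 remains adequate. Likelihood on all available data is itself unbiased only under missing at random.

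**What to change.** Replace the scope phrase in section 2.7 with a statement to this effect:

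- All participants with at least one measurement enter the mixed model, fitted by maximum likelihood to all available waves, assuming data are missing at random given group, earlier scores and the background variables included in the model. Those variables should be listed.
- If multiple imputation is used, it also imputes the missed waves of dropouts, separately by arm.
- One of the two methods is named as primary.
- The four-wave completer analysis is kept as a sensitivity analysis.

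Reconcile this wording with the exclusion of programme non-completers in section 2.3, because an all-participants statement and that exclusion cannot both stand unqualified. The cost is wording only: the model and software are already in the plan, and no additional data are needed. The change should be made before the analysis.
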